## Abstract

**Background:**

Meniscectomy is a risk factor for knee osteoarthritis, with increased medial joint loading a likely contributor to the development and progression of knee osteoarthritis in this group. Therefore, post-surgical rehabilitation or interventions that reduce medial knee joint loading have the potential to reduce the risk of developing or progressing osteoarthritis. The primary purpose of this randomised, assessor-blind controlled trial is to determine the effects of a home-based, physiotherapist-supervised neuromuscular exercise program on medial knee joint load during functional tasks in people who have recently undergone a partial medial meniscectomy.

**Methods/design:**

62 people aged 30–50 years who have undergone an arthroscopic partial medial meniscectomy within the previous 3 to 12 months will be recruited and randomly assigned to a neuromuscular exercise or control group using concealed allocation. The neuromuscular exercise group will attend 8 supervised exercise sessions with a physiotherapist and will perform 6 exercises at home, at least 3 times per week for 12 weeks. The control group will not receive the neuromuscular training program. Blinded assessment will be performed at baseline and immediately following the 12-week intervention. The primary outcomes are change in the peak external knee adduction moment measured by 3-dimensional analysis during normal paced walking and one-leg rise. Secondary outcomes include the change in peak external knee adduction moment during fast pace walking and one-leg hop and change in the knee adduction moment impulse during walking, one-leg rise and one-leg hop, knee and hip muscle strength, electromyographic muscle activation patterns, objective measures of physical function, as well as self-reported measures of physical function and symptoms and additional biomechanical parameters.

**Discussion:**

The findings from this trial will provide evidence regarding the effect of a home-based, physiotherapist-supervised neuromuscular exercise program on medial knee joint load during various tasks in people with a partial medial meniscectomy. If shown to reduce the knee adduction moment, neuromuscular exercise has the potential to prevent the onset of osteoarthritis or slow its progression in those with early disease.

**Trial Registration:**

Australian New Zealand Clinical Trials Registry reference: ACTRN12612000542897

## Background

Osteoarthritis (OA) is a common musculoskeletal disease that is considered by the World Health Organisation as one of the ten leading causes of disease burden in high-income countries [1]. The knee is the most commonly affected lower limb joint [2]. Osteoarthritis is associated with pain, reduced physical function and high economic costs [3-5]. Given there is no cure for OA, it is widely recognised that OA prevention, particularly targeting groups at greater risk of developing the condition, is an important research priority to reduce the personal and societal disease burden [6]. Individuals who have undergone an arthroscopic partial meniscectomy (APM), a common surgical procedure for meniscal injury particularly involving the medial meniscus [7], constitute one such group at risk of tibiofemoral knee OA [8]. Meniscal tears can be categorised as traumatic or degenerative tears. Traumatic tears are typically longitudinal tears and result from an acute sports-related injury in young active individuals [9,10]. Alternatively, degenerative tears are generally observed as horizontal-cleavage lesions or flap tears [11] in middle-aged and older populations [10]. These degenerative tears are suggested as the first sign of knee OA [12]. In fact, it is estimated that 50% of individuals have radiographic signs of knee OA within 10–15 years following meniscectomy [12-14]. Moreover, accumulating magnetic resonance imaging (MRI) data suggest that structural changes begin soon after APM. Studies have observed an increase in cartilage loss over 2 years following APM [15], and a greater prevalence of cartilage defects between 3 months and 4 years post-APM [16] as compared to healthy controls. Furthermore, medial femoral cartilage integrity as measured by glycosaminoglycan (GAG) content was impaired 4 years following medial APM when compared to the reference lateral femoral condyle cartilage [17]. These findings highlight the urgent need to develop and evaluate rehabilitative interventions that may reduce the likelihood of OA development in this patient group.

The onset of knee OA following APM may be partly related to a higher distribution of medial knee joint load. The external knee adduction moment (KAM), is a widely used biomechanical marker of medial knee load distribution measured via three-dimensional gait analysis. Indeed a large cross-sectional study reported that individuals 3-months post-APM surgery had ~18% higher peak KAM bilaterally as compared to healthy controls during walking [18]. This highlights the greater medial distribution of knee joint load during walking in patients’ post-APM. The finding of higher medial joint load distribution post-APM is relevant to the pathogenesis of knee OA. The peak KAM is generally higher in those with established structural medial knee OA than in healthy controls [19-22] and also correlates with knee OA severity as measured on radiographs [21,23]. Furthermore, longitudinal studies have associated the peak KAM with the development of chronic knee pain in older people [24] as well as an increased risk of radiographic OA progression in those with established disease [25]. A greater KAM impulse, which takes into account the average magnitude and duration of medial loading throughout stance and may be a more sensitive marker of medial joint dynamic loading than peak KAM [26], has also been related to cartilage degradation in people following APM [27] and in those with knee OA [28]. Thus, it is apparent that medial knee joint loading (as inferred by KAM parameters) is associated with the pathogenesis of knee OA and if reduced, could potentially prevent or delay OA-initiation and progression in people following APM of the medial meniscus.

Exercise may be an effective strategy to reduce the greater medial knee joint load distribution observed post-APM. Exercise is recommended as part of rehabilitation post-meniscal surgery [29] and is also an attractive rehabilitation option considering that it is relatively safe, is a patient-driven strategy that can facilitate long-term self-management, is inexpensive and is clinically advocated in knee OA management [30,31]. There is limited evidence as to the effects of different exercise types on knee joint loading. Studies have examined the effects of knee and hip muscle strengthening [32-34] on medial knee joint loading in older patients with established symptomatic and radiographic knee OA. Despite improving OA-associated symptoms, no change in medial knee joint loading was found during walking with the tested strengthening programs [33,34]. However, some pilot evidence suggests that neuromuscular exercise may reduce loading across the knee joint in people with and without knee OA during more functionally challenging tasks than walking [35,36].

Neuromuscular training is a broad term used to incorporate many components of exercise training including: balance, perturbation, agility, plyometrics, strength and endurance [37,38]. Furthermore, neuromuscular training programs are designed with various aims: to prevent sports injuries in young athletes [39], to rehabilitate individuals post-sport related injuries [40] and more recently to prevent OA progression [37]. Therefore it is important to acknowledge that a vast array of exercises and intensities are considered neuromuscular in nature. However, regardless of the target population or aim of the training program, a common feature of neuromuscular training is the use of functional weight-bearing exercise positions. Physiologically, neuromuscular training aims to enhance the unconscious motor response by calling upon both afferent signal and central mechanisms responsible for dynamic control [41]. A randomised controlled trial (RCT) reported that following a 4-month neuromuscular training program, participants post-APM improved one-leg hop for distance and improved self-reported outcomes [17,42]. Importantly, this RCT also found improved cartilage quality as indicated by the GAG content on MRI following the neuromuscular exercise program [43]. Neuromuscular training has been found to reduce external abduction knee loads in young healthy females while landing from a jump [35] adding support to the premise that neuromuscular exercise can alter frontal plane moments. Of particular relevance to the current study is evidence that peak KAM can be reduced with neuromuscular exercise in middle-aged individuals with moderate levels of knee OA [36]. This uncontrolled pilot study included 13 individuals and found a 14% reduction in peak KAM during a one-leg rise task with no difference in peak KAM during walking following the 8-week training period. Despite the difference in the purposes of the neuromuscular exercise training programs [35,36], these findings from healthy and OA cohorts suggest that neuromuscular training has potential to reduce frontal plane knee moments. Furthermore, these studies suggest that potential alterations in knee joint load distribution appear to be detected during more challenging motor tasks following neuromuscular training. This hypothesis is further supported by recent cross-sectional evidence in APM individuals describing altered neuromuscular function during a forward lunge [44] that were not detected during stair descent when comparing the operated and non-operated legs [45].

Given that neuromuscular training has the potential to alter knee joint load, we hypothesise that neuromuscular training may be an effective load-modifying intervention to rehabilitate individuals post-APM, a patient group at risk of developing knee OA. However to date, this has not been evaluated. The primary objective of this study (‘SCOPEX’) is to determine whether a neuromuscular exercise program (‘ALIGN’) reduces medial knee joint loading in people with a recent medial APM, as measured by the peak external KAM during normal pace walking and one-leg rise. The secondary objectives are to evaluate the effect of the ALIGN program post-medial APM on: i) the peak external KAM during fast pace walking and one-leg hop for distance; ii) the external KAM impulse during: walking (normal pace and fast pace), one-leg rise and one-leg hop for distance; iii) knee and hip muscle strength; iv) electromyographic muscle activation patterns; v) functional physical performance and vi) patient-reported outcomes knee pain, other symptoms, activities of daily living, sport and recreation and knee-related quality of life.

### Primary hypothesis

The 12-week neuromuscular exercise program will reduce medial knee joint loading, as characterised by the peak external KAM during normal pace walking and one-leg rise, when compared to a control group not receiving the neuromuscular exercise program.

### Secondary hypotheses

The 12-week neuromuscular exercise program will: i) reduce the peak external KAM during fast-pace walking and one-leg hop for distance; ii) reduce the external KAM impulse during walking (normal and fast pace), one-leg rise and one-leg hop for distance; iii) improve knee and hip muscle strength; iv) alter electromyographic muscle activation patterns; v) improve functional physical performance; vi) improve self-reported outcomes (knee pain, other symptoms, activities of daily living, function, sport and recreation function and knee-related quality of life) when compared to a control group.

## Methods

### Trial design

This will be an assessor-blinded, randomised controlled trial of a 12-week physiotherapist-supervised and home-based neuromuscular exercise intervention. Assessment will be performed at baseline and immediately following the intervention (12 weeks). The protocol conforms to CONSORT guidelines for non-pharmacological studies [46] (Figure 1) and has been registered with the Australia and New Zealand Clinical Trials Registry prior to study commencement.

**Figure 1 F1:**
[figure not shown]
**Trial Protocol**
.

### Participants

Sixty-two participants with a recent isolated medial APM will be recruited from metropolitan Melbourne, Australia. The primary recruitment strategy will be via screening of surgical records of several Melbourne-based orthopaedic surgeons. Additionally, we will recruit individuals by advertising through University staff newsletters and Facebook. To be eligible, participants must be aged between 30–50 years and have undergone an isolated medial APM in the past 3–12 months.

The exclusion criteria are:

i) an average overall pain severity ≥3 out of 10 on an 11 point numerical rating scale in the past week

ii) signs of moderate to severe radiographic knee OA (Kellgren-Lawrence grade >2) [47]

iii) full tears of the anterior or posterior cruciate knee ligaments

iv) anterior or posterior ligament reconstructions

v) spinal or lower extremity pain (other than the affected knee) that limits everyday activities or required treatment in the past month

vi) high levels of physical activity defined as participation in an organised team or individual sport that requires regular competition and requires some form of systematic training [48]

vii) history of lower limb surgery (other than knee arthroscopy)

viii) other form of arthritis, diabetes, cardiac circulatory conditions that limit everyday activities (as determined by the Self-administered Co-morbidity Questionnaire)[49]

ix) neurological condition such as Parkinson’s disease, multiple sclerosis or stroke

x) any condition precluding safe participation in exercise

(xi) unable to complete the study protocol

(xii) inadequate written or spoken English

### Procedure

Individuals who meet the inclusion criteria will be sent information in the mail. Approximately two weeks later these individuals will be contacted by telephone and invited to undergo further screening for exclusion criteria. Screening records will be maintained to detail the criteria eliminating individuals found to be ineligible. Following further screening for exclusion criteria via telephone, people who are potentially eligible will undergo a semi-flexed standing postero-anterior x-ray of their partially meniscectomised knee at one of three trial radiology centres (unless they can provide their own radiographs taken within the past 12 months). The x-rays will be graded by one of two experienced clinicians. Eligible participants will attend the Centre for Health Exercise and Sports Medicine (CHESM) at The University of Melbourne for baseline and follow-up testing. Following baseline testing, participants will be randomised into one of two groups: i) neuromuscular exercise training; or (ii) no neuromuscular exercise training. The 12-week neuromuscular exercise training intervention will include 8 individual physiotherapist visits: twice in the first week, one in each of the second and third weeks and fortnightly thereafter. Participants in this group will also perform a home-based exercise program throughout the 12-week intervention. All participants will provide written informed consent.

### Blinding

Baseline and follow-up assessments will be performed by the same outcome assessor who will remain blinded to group allocation and who will not be involved in providing the neuromuscular exercise program. Furthermore, the outcome assessor will not visit any of the physiotherapist centres. Participants will be instructed not to disclose details about their group allocation to the blinded assessor. By virtue of the design, it is not possible to blind the participants or the physiotherapists.

### Randomisation and allocation concealment

A researcher with no other involvement in the study will prepare the randomisation schedule *a priori* using a computer generated random numbers table. Randomisation will be conducted by random permuted blocks of size 6 to 8 and stratified by gender. To conceal randomisation, the same independent researcher will prepare consecutively numbered, sealed opaque envelopes. The envelopes will be kept in a locked location and only accessible to the independent researcher responsible for randomising participants following baseline testing. Another independent researcher will then schedule the first two physiotherapist appointments for those in the neuromuscular exercise group.

### Intervention

Participants will be asked to refrain from seeking other forms of treatment during the trial. Additionally, participants from both groups will be asked to refrain from performing additional physical activity to what they currently perform. Analgesia will be permitted as required.

### Neuromuscular exercise group

Similar to previous neuromuscular exercise programs described for knee OA patients [37,38], our neuromuscular exercise program, ALIGN, is based on biomechanical and neuromuscular principles that aim to improve sensorimotor function. Considering that the context of the current study is OA prevention and delay of progression, participants will be instructed to focus neutral alignment of the hip, knee and foot during weight bearing positions. Furthermore, participants will also be encouraged to focus on the performance quality of each exercise. The neuromuscular exercise intervention, ALIGN will target muscles of both lower limbs. The exercises were selected based on previous research demonstrating these exercises or similar variations to have reduced medial knee joint load, improved cartilage quality and physical function in people at risk of developing or progressing established knee OA [36,42,43].

### Study physiotherapists

Twelve physiotherapists in private practices at multiple locations throughout metropolitan Melbourne, Australia will deliver the neuromuscular exercise program titled “ALIGN”. The physiotherapists have an average of 15 years (range 3–36 years) of clinical experience since qualification and 11 years (range 0–27) of post-graduate clinical musculoskeletal experience. Three (25%) have a postgraduate Masters qualification in sports or manipulative/musculoskeletal therapy. The physiotherapists will attend a 3-hour training session addressing the delivery of the neuromuscular exercise program and receive a detailed treatment manual. This large number of study physiotherapists is necessary for feasibility and to improve the generalisability of study findings. Physiotherapists will be supplied with equipment for their clinics to demonstrate the exercises to participants. Participants will choose a project physiotherapist to attend based on their geographical location and time availability. Training will commence within one week of baseline assessment.

### First physiotherapist visit

The initial visit with the physiotherapist will last 45 minutes, during which participants will be educated about the goals and benefits of the neuromuscular exercise program. Potential barriers to exercise will also be addressed. Individuals with knee OA have expressed that pain or the fear of pain prevents exercise participation [50]. Therefore, participants will use a pain monitoring scale to guide their home exercises, where zero represents “no pain” and ten represents “worst possible pain”. On this scale, exercising with a pain score up to two is considered ‘safe’, exercising with pain up to five is considered ‘acceptable’ and exercise when pain scores are above five is deemed ‘high risk’ [51]. However, due to the minimal levels of pain in this cohort, we do not anticipate that pain will be an issue. Nonetheless, it is thought that monitoring knee pain before and after each exercise session will give participants confidence to exercise. Another commonly expressed barrier to exercise is lack of time [52]. During the first session, physiotherapists will encourage participants to consider how they can best fit the neuromuscular exercise sessions into their weekly schedule. Following the initial education and discussion of exercise barriers, participants will be taught their individualised training program by the physiotherapist. The 6 core exercises in the ‘ALIGN’ program are described in Table 1. Physiotherapists will determine the appropriate starting level of each exercise for individual participants based on the quality of performance by the participant and the verbalised degree of difficulty from participants.

**Table 1 T1:** Neuromuscular exercise program; ALIGN

**Exercise**	**Primary Muscles Targeted**	**Description of starting level**
**A**bdominal crunches	Abdominal muscles	Performed in supine with knees flexed on exercise ball, participants perform abdominal crunches
bridge	Hamstrings, gluteals, hip adductors	Performed in supine with knees flexed on the exercise ball, participants rise up and hold the position with a towel between knees
**L**unge	Gluteals, knee extensors and flexors	Standing upright, participants lunge forward and return to starting position
**I**ncomplete circle	Hip abductors	Performed in a unipedal stance while the opposite limb rotates in a semi-circular motion
**G**et tapping	Knee extensors and hip abductors	Performed in a unipedal stance on a stepper, as the opposite leg taps the ground behind the step
k**N**ee bends	Knee extensors, gluteals and hip abductors	Performed in a bipedal stance in front of a chair with feet hip width apart, knees are bend so the bottom nearly touches the chair or heels remain in full contact with the floor

### Home training sessions

Participants will be instructed to perform their individualised neuromuscular exercises at home three times per week in addition to exercises performed during scheduled supervised physiotherapy visits. Each session will last approximately 30–35 minutes, accumulating to a total of >90 mins of exercise per week. Despite there being no specific guidelines for neuromuscular training, based on the authors’ experience and the American College of Sports Medicine recommendations for neuromotor exercise, (2–3 days per week; 20–30 minutes each day) [53], it was considered that >90 minutes per week would be adequate for physiological adaptations.

### Follow-up physiotherapist sessions

During the subsequent seven physiotherapist sessions each lasting 30 minutes, physiotherapists will assess adherence to the home exercise program by reviewing the participants’ weekly logbook and inquiring about any adverse events experienced. Physiotherapists will then assess exercise technique and increase the exercise intensity (in terms of the level) as necessary. Exercise progression will be based on the physiotherapists’ assessment of the quality of the exercise performance and on the participant’s reported pain response and degree of difficulty experienced. Varying surfaces and weight will be used to increase the exercise difficulty. The 6 core exercises and respective levels of difficulty are detailed in an Additional File. During the period between physiotherapy visits, participants are also encouraged to progress by increasing the volume of the repetitions and sets. Participants will start performing 2 sets of 12 repetitions. Participants can progress their training by opting to increase the volume to 2 sets of 15 repetitions; 3 sets of 12 repetitions and 3 sets of 15 repetitions respectively. However, the level of difficulty is, as previously described, increased by the physiotherapist. Physiotherapists will maintain standardised treatment notes.

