### Control group

Participants in the control group will not receive any interventions during the 12-week study period.

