**Other measures**	
Peak external knee flexion moment	3-dimensional movement analysis
Dynamic tibial alignment, lateral trunk lean angle, internal foot rotation angle	3-dimensional movement analysis
Static alignment	Inclinometer
Disease severity	X-ray (baseline)
Physical activity levels	Lower Extremity Activity Scale
Adverse events	Participant log-book (follow-up)
Adherence to exercise program	Participant log-book (follow-up)
Treatment session attendance	Therapist treatment records (intervention group only) (follow-up)

All measures are obtained at baseline and 13 weeks, unless otherwise indicated.

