### Other measures

A clinical measure of static knee alignment will be taken using an inclinometer [62]. Participants will be asked to stand comfortably, after which the tibial angle will be measured with respect to the vertical. This measure has been shown to be reliable (ICC = 0.94) and valid in relation to mechanical axis from full-length radiographs (r = 0.80) [62]. Physical activity will be measured using the Lower Extremity Activity Scale (LEAS), which will provide a global indication of physical activity level. From a series of options, participants select one option that best describes their current physical activity level. The LEAS is used in OA populations and has been found to be reliable and valid [63]. Participant adherence to the neuromuscular exercise program will be obtained by recording the number of physiotherapy sessions attended (out of a maximum number of eight). Participants will maintain a logbook to record the number of home exercises completed during the 12-week intervention period. For the purpose of this study, we will consider good adherence as: 1) at least 80% of physiotherapy sessions attended (i.e. 6 physiotherapy visits) and 2) at least 80% of the training sessions completed (i.e. 29 training sessions). Physiotherapists will also indicate their perceived impression of the participant’s overall adherence to the treatment on an 11-point numeric rating scale, with 0 representing ‘not at all and 10 being ‘completely as instructed’ [64].

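### Adverse events are actively asked about only in the exercise arm, so any comparison of event counts between arms would be at risk of detection bias

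*Protocol article*

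**What the plan says.** **Exercise arm.** The Procedure section schedules "8 individual physiotherapist visits: twice in the first week, one in each of the second and third weeks and fortnightly thereafter". Under Follow-up physiotherapist sessions, the work of the later visits is introduced with "During the subsequent seven physiotherapist sessions each lasting 30 minutes". It includes reviewing the participant's weekly logbook and "inquiring about any adverse events experienced". The section on the first physiotherapist visit adds that exercisers monitor knee pain around each exercise session.

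**Control arm.** "Participants in the control group will not receive any interventions during the 12-week study period". Trial design gives the time points common to both arms: "Assessment will be performed at baseline and immediately following the intervention (12 weeks"). No contact with controls between these two points is described.

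**Source of the data.** Table 2 places adverse events under other measures, with the source "Participant log-book (follow-up"). The text under Other measures describes this log-book as follows: "Participants will maintain a logbook to record the number of home exercises completed during the 12-week intervention period". The items that Self-reported measures adds at follow-up are a pain rating, perceived change in physical function, and treatment experience. Adverse events are not among them.

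**Analysis.** Adverse events appear in no objective or hypothesis, and nowhere under Data and statistical analysis.

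**The concern.** How many adverse events a trial records depends on how often and how directly participants are asked. Here one arm is asked face to face, repeatedly, by a clinician who has the participant's diary at hand. For the other arm no prompt is described. Minor events such as a short flare of knee pain or muscle soreness can be expected in both arms after a meniscectomy, but as described they would be recorded more completely in one.

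Adverse events are a listed measure in a two-arm randomised trial, so readers will tend to set the two counts side by side. A raw comparison would tend to make the programme look more harmful than it is. If only exercise-arm events are reported, there is no control rate against which to judge background symptoms. The Discussion expects the trial, if positive, to support a feasible rehabilitation option, and the primary outcome is a biomechanical marker. Comparable harm data would bear on any such recommendation.

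**Working it through.** **1. Number of active enquiries.** From the visit schedule in Procedure: 2 (week 1) + 1 (week 2) + 1 (week 3) + 4 fortnightly (weeks 5, 7, 9 and 11) = 8 visits. Subtracting the first visit, 8 − 1 = 7 follow-up sessions. This agrees with the seven stated under Follow-up physiotherapist sessions. The contrast is therefore seven described enquiries in the exercise arm against none described in the control arm.

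**2. Does Table 2 show collection in controls?** The attendance row is limited to one arm: "Therapist treatment records (intervention group only) (follow-up"). The adverse event row carries no such limit, which might suggest that controls keep a log too. But the row for adherence to the exercise program has the same log-book source and is also unmarked, although adherence can apply only to the exercise arm. The missing mark therefore does not settle whether controls are covered. The only log-book content described is home exercises, which controls do not have. Even if controls did hold a log-book, no one is described as reviewing it with them during the 12 weeks.

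**3. Possible size, by assumption only.** The article gives no event rate and no capture rate. Let p be the true risk, equal in both arms. Assume full capture in the exercise arm and a fraction c captured among controls. Then

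apparent risk ratio = p / (c × p) = 1 / c.

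The true risk cancels, so the ratio depends on nothing but the assumed relative capture. For expected counts I use the planned 31 per group (Sample size) and p = 20% as an assumed middle value:

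| Control capture c | Apparent risk ratio | Expected events, exercise (31 × 0.20) | Expected events, control (31 × 0.20 × c) |
|---|---|---|---|
| 80% | 1 / 0.8 = 1.25 | 6.2 | 5.0 |
| 60% | 1 / 0.6 = 1.67 | 6.2 | 3.7 |
| 40% | 1 / 0.4 = 2.5 | 6.2 | 2.5 |

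With p = 10% the expected counts are 3.1 against 2.5, 1.9 or 1.2. With p = 30% they are 9.3 against 7.4, 5.6 or 3.7. The ratios do not change.

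**The case against.** The strongest reply has four parts.

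- **No comparison is planned.** A reader might infer that the trial has a between-group safety comparison and that it is biased. The article does not support this: no objective, hypothesis or analysis statement names one. This stands, and the point is conditional on counts being compared.
- **The article is condensed.** The enquiry is part of how a session is conducted, Table 2 names the log-book and not the physiotherapist as the source, and procedures for controls may be in the full protocol. A reader might infer that control events are not collected at all; the article does not say so. This also stands, so the contrast is with no contact *described*. But the point does not rest on missing detail alone. The article states a method of collection, and as stated that method differs between arms.
- **Symmetric data on harm already exist.** A reader might infer that the trial could say nothing about harm. That goes too far. The KOOS at baseline and follow-up, and the pain rating and perceived change in function at follow-up, are not limited to one arm. They give evidence on persistent worsening. They do not count transient events over the preceding weeks.
- **A common questionnaire does not equalise recall.** After seven prompts and weekly diary keeping, exercisers may remember more. This is a fair limit on the remedy.

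**Conclusion.** The asymmetry is in the text: seven active enquiries in the exercise arm, none described for controls, and a listed source described only as an exercise log. A comparison of adverse event counts would be at risk of detection bias towards more events in the exercise arm. The direction is clear, but the size cannot be computed from the article. The risk ratios of 1.25 to 2.5 simply restate the assumed control capture of 80% to 40%; they are not estimates for this trial. The conclusion assumes that controls have no undescribed prompting of similar intensity. If the full protocol provides it, the concern falls away. The primary and secondary efficacy analyses are not affected.

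**What to change.** At the existing follow-up assessment, have both arms complete the same self-administered adverse event item covering the past 12 weeks. Word it so that it does not reveal the arm to the blinded assessor. Base any between-arm comparison on that item, read alongside the KOOS and the pain rating. Report events found through physiotherapist enquiry or the exercise log separately, as descriptive data for the exercise arm. State whether control participants keep a log-book.

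The cost is one short item at a visit that already takes place, with no extra visit or staff. Recall over 12 weeks will miss minor events, and earlier prompting may leave recall somewhat better in the exercise arm. The bias is therefore reduced rather than removed, and the report should say so.
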